#### Control group

2.3.3.

Participants will receive CBT4CBT with their reinforcers contingent on submitting blood samples, not PEth results. Blood sample collection will occur on a fixed schedule of once weekly (Weeks 1-4), then every other week (Weeks 6 and 8), followed by every four weeks (Weeks 12, 16, 20, and 24), and a last intervention visit occurring on Week 26 (see Fig. 1). Similar to previous studies, the amount of reinforcement allotted for each sample will be a base level of $20 or yoked to the CM group [23,24]. When Control participants submit a blood sample, they will receive a reinforcer amount that is equal to the average provided to CM participants during the previous month, resulting in earnings that approximate the CM group. For example, if the average earning per sample in the CM group was $50, Control participants will receive $50 for each sample submitted. Total Control group reinforcement could be as high as $1,820 but is expected to be 50% of that amount.

### Data collection

2.4.

Staff will collect data via Zoom at enrollment, randomization, treatment (Weeks 1–26), and follow-up visits (Weeks 30, 38, 52, 78). Measures that occur asynchronously will include the TestMyBrain cognitive tests and ANA questionnaire. The enrollment visit will take approximately three hours, while the randomization visit will take one hour. Weekly visits during the Starting Phase will average thirty minutes, while Sustaining Phase and follow-up visits will take an hour. Blood and urine samples will be collected at each visit in addition to the measures outlined in Table 1. Participants will receive $30 for the enrollment visit, $10 for the randomization visit, and $20 for each follow-up visit. To ensure timely submission of blood samples, all participants will receive a $10 bonus per sample if they ship the same day as their study visit. Compensation provided during the treatment phase is outlined in Section 2.3.

### Measures

2.5.

#### PEth sample collection and analyses

2.5.1.

Staff will mail study kits to participant residences. The kit will include a TASSO-M20 device for blood collection, isopropanol swabs, towelettes, a bandage, a urine cup, a uEtG dipcard, and a pre-paid shipping envelope. The TASSO-M20 device will be pre-labeled with the participant study ID and the visit number. Participants will self-collect blood from the upper arm with the TASSO-M20 device while videoconferencing with staff. Participants will press a button on the device to create a small lance in the skin, from which capillary blood will fill four plugs in the device (20 μL ± 5%/plug) over the span of five minutes (see tassoinc.com). Once completed, participants will remove the device, take the film cover over the plugs off to allow air drying, and seal the device in a prepaid FedEx envelope. Participants will mail the packet to the University of Texas Health San Antonio for PEth analysis. Our pilot study demonstrated that the TASSO-M20 device is a feasible method for collecting blood, e.g., consistency of blood volume collected, easy for participants to use, minimal pain [7].

PEth 16:0/18:1 levels will be assessed using a modified method for high-performance liquid chromatography with tandem mass spectrometry [25,26]. All reagents will be purchased from Thermo Fisher Scientific and Sigma Chemical (Fisher Scientific, Waltham, MA). PEth 16:0/18:1 analytical standard will be purchased from Cerilliant (Round Rock, TX). Deuterated PEth (16,0/18,1-*d*5, Echelon Biosciences, Salt Lake, UT) will serve as the internal standard. PEth calibrator (0–2000 ng/mL) and control samples will have a volume of 40 μL. Two plugs from each TASSO-M20 device will be analyzed. Each sample, excluding the blank control, will be spiked with 10 μL of the 0.1 μg/mL deuterated PEth, final concentration 25 ng/mL. PEth will be extracted from the calibrator, control, and experimental samples by the addition of isopropanol (1 mL) with vortexing (1 min), shaking at high speed (45 min, Eberbach Shaker), sonication using 5 second bursts (Q-Sonica, 10% max), and centrifugation at 3,200 g at 4°C (30 min). The clear supernatants will be transferred to new tubes and evaporated to residue with a gentle stream of nitrogen at 30 °C. The residues will be dissolved in 100 μL of a 1:1 resuspension solution of mobile phase A (40,60, 2 mM ammonium acetate,acetonitrile) and mobile phase B (isopropanol) and then transferred to 1.5 mL snap-cap polypropylene microcentrifuge tubes and centrifuged for 10 min (3,200 *g*) at 4°C. The eluted samples will be transferred to 300 μL polypropylene autosampler vials and then 10 μL will be injected into the HPLC/MS/MS system. The ratio of peak areas of PEth 16:0/18:1 to that of d5-PEth 16:0/18:1 of the unknown samples will be compared against a linear regression of ratios of calibrators from 0 to 4,000 ng/mL.

#### Urine ethyl-glucuronide (uEtG)

2.5.2.

uEtG will be assessed at each visit using a dipcard (≥300 ng/mL threshold, Healgen Scientific). Participants will self-collect urine samples off camera using a point-of-care immunoassay cup that assesses substances other than alcohol (see Section 2.5.4). Participants will conduct the uEtG dipcard test on camera with study staff assistance.

#### Self-reported alcohol use

2.5.3.

Self-reported daily alcohol use will be assessed at each visit using the Alcohol Timeline Followback (ATLFB) [27]. This information will reflect the thirty days prior to the enrollment visit, as well as “since the last visit” at each subsequent visit. Additionally, we will record hours since the last drinking episode and the number of drinks at the last drinking episode.

#### Alcohol-associated harms

2.5.4.

Self-reported cigarette use will be assessed per Timeline Followback, and nicotine dependence assessed using the Fagerstrom Test for Nicotine Dependence. The use of costly medical care (non-study related resources) will also be measured using the Non-study Medical and Other Services (NMOS) form, which captures self-reported healthcare utilization for inpatient, outpatient, and emergency department visits, inpatient, residential, and outpatient treatment days, mental health treatment visits, and substance use disorder medications [30–32]. Lastly, a urine point-of-care immunoassay cup will be used to assess uEtG and cannabis use (tetrahydrocannabinol ≥50 ng/mL; UScreen).

#### ANA framework

2.5.5.

The ANA will serve as our conceptual framework to identify pre-intervention (e.g., executive functioning, incentive salience, negative emotionality) and in-treatment (e.g., alcohol abstinence) factors related to post-treatment outcomes over the 12-month follow-up period [28]. We will use the validated 15-item self-report measure of ANA constructs [29], in addition to administering performance-based measures of executive functioning (i.e., divided attention, working memory, mental flexibility, response inhibition, impulsivity, and delayed discounting). Performance-based measures will be self-administered remotely using the TestMyBrain.org platform [30].

#### Economic measures

2.5.6.

The NMOS form will be used to measure resource utilization needed to inform the state-policymaker and societal perspectives, including criminal-legal, social safety-net, labor/school productivity, travel time to medical care, and caregiver time. This form utilizes time-anchoring methodology to assess participant resource use over the 30 days prior to the enrollment visit, and then “since your last visit” at each subsequent administration. The Drug Abuse Treatment Cost Analysis Program instrument will be used to guide the microcosting analysis (see 3.3.2) [31].

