#### CM group

2.3.2.

Participants will receive CBT4CBT in addition to their reinforcers being contingent on PEth results. The criteria for PEth-verified abstinence will differ depending on the treatment phase. During the Starting Phase, week-over-week decreases in PEth levels, regardless of the amount, will be reinforced until participants reach PEth <20 ng/mL, which is consistent with approximately four weeks of abstinence. After completing 4 weeks of the Starting Phase and/or achieving PEth <20 ng/mL, participants will transition to the Sustaining Phase with visits every two to four weeks, as long as abstinence is maintained. Should PEth levels indicate that drinking occurred since the last visit (≥20 ng/mL), CM participants will return to the Starting Phase with weekly visits until PEth levels once again indicate abstinence (see Fig. 2). Returning to the Starting Phase provides CM participants with additional support when a drinking episode occurs. Participants will continue the Sustaining Phase when their PEth levels return to abstinence (<20 ng/mL), and treatment duration will remain 26 weeks regardless of how long a participant remains in the Starting Phase or how many times they return to the Starting Phase.

During the Starting Phase, participants will receive $20 for the first PEth result that indicates reduced alcohol consumption (i.e., week-to-week decrease). They will then receive an additional $5 for every week of consecutive abstinence (i.e., week-to-week decrease during the Starting Phase, <20 ng/mL during the Sustaining Phase). PEth-positive samples (i.e., week-to-week PEth increase, PEth ≥20 ng/mL) will result in reinforcers being withheld until the next negative test, for which the participant will earn $20. A subsequent negative test will then reinstate the total reinforcers earned prior to testing positive, plus an additional $5. For example, if a participant previously earned $40 but then tests positive, they will receive $0 at the current visit. When the participant submits the next negative sample, they will earn $20, and then be eligible for reinstating their highest earned total (e.g., $40) plus an additional $5 when they have two consecutively negative samples. This reinforcer escalation schedule, reset, recovery approach is consistent with previous CM studies [21,22].

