#### Economic analyses

3.3.2.

Economic analyses will examine resource use from the healthcare sector, state-policymaker, and societal perspectives [34–36]. The healthcare-sector perspective includes medical costs incurred by the system on behalf of participants, including the cost of interventions, and participant out-of-pocket costs. The state-policymaker perspective informs resource allocation decisions made in the interest of the public, who are responsible for funding healthcare for many individuals with AUD, as well as criminal-legal resources, and social safety-net programs. The societal perspective accounts for all resources utilized by, or on behalf of, individuals with AUD, including those mentioned above, and those more broadly associated with untreated or undertreated AUD and comorbid conditions, such as premature mortality, reduced labor productivity, and costs incurred by crime victims [34,37].

First, microcosting analyses will be conducted to identify resource use and estimate the costs associated with implementing and sustaining CM relative to the Control condition. Next, between-arm difference in predicted-mean costs will be calculated according to each stakeholder perspective over the intervention and follow-up periods. The resource costing method will be used to assign national real-world unit costs to each resource utilized. Then, between-arm differences in predicted-mean values for effectiveness measures, alcohol-free years and quality-adjusted life-years (QALY), will be calculated for each time period with generalized linear mixed-models to adjust for potential confounding factors. Finally, incremental cost-effectiveness ratios (ICERs) will be calculated for each perspective/effectiveness measure by time period, and cost-effectiveness acceptability curves estimated to assess the uncertainty surrounding each ICER.

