**Fig. 2. F2:**
[figure not shown]
CM Treatment Schedule: CM participants will remain in the Starting Phase for the first four weeks of treatment or until their PEth levels indicate abstinence (<20 ng/mL). They will then transition to the Sustaining Phase of treatment, where they are reinforced for maintaining PEth levels below 20 ng/mL. Should a participant in the Sustaining Phase have a PEth level ≥20 ng/mL, they will return to weekly visits (i.e., Starting Phase). Once PEth levels are again <20 ng/mL, participants will return to monthly visits in the Sustaining Phase. Regardless of how many times a participant returns to the Starting Phase, the treatment duration will remain 26 weeks.

**Table 1 T1:** Study measures and data collection schedule: See methods for a description of each measure. Acronyms included are phosphatidylethanol (PEth), urine ethyl glucuronide (uEtG), Non-study Medical and Other Services (NMOS), Drug Abuse Treatment Cost Analysis Program (DATCAP), Client Satisfaction Questionnaire (CSQ-8), and the Sweating, Hallucinations, Orientation, Tremor scale (SHOT).

Measure	Enrolment Visit	Every Visit	Treatment Visits Week 4, 8, 12, 16, 20, 26	Follow-Up Visits Week 30, 38, 52, 78
Eligibility Criteria	✓			
Demographics	✓			
PEth-Defined Abstinence <20 ng/mL	✓	✓		
PEth-Defined Excessive Drinking ≥ 200 ng/mL	✓	✓		
uEtG-Defined Recent Drinking: ≥ 300 ng/mL	✓	✓		
Self-Reported Alcohol Timeline Followback	✓	✓		
Self-Reported Cigarette Timeline Followback	✓	✓		
Nicotine dependence: Fagerstrom	✓		✓	✓
Drug Use: 5-Panel Cup	✓	✓		
ANA Model: Questionnaire	✓	✓		
ANA Model: TestMyBrain	✓			
Healthcare Utilization: NMOS	✓		✓	✓
Intervention cost: DATCAP	✓			
Attrition: Percent missed visits		✓		
Client Satisfaction: CSQ-8			Weeks 4, 26	
Alcohol withdrawal: SHOT	✓	✓		
Adverse Events	✓	✓		

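### The NMOS recall window is anchored to the last visit, but the form is given at only some treatment visits, so read literally it under-records resource use unequally between arms

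*Protocol article*

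**What the plan says.** - **Recall window** (Protocol article, 2.5.6 Economic measures): "30 days prior to the enrollment visit, and then “since your last visit” at each subsequent administration".
- **When the form is given** (Table 1): the row "Healthcare Utilization: NMOS" is ticked for enrollment, for the column "Treatment Visits Week 4, 8, 12, 16, 20, 26" and for the column "Follow-Up Visits Week 30, 38, 52, 78". It is not ticked under the every-visit column.
- **Control visits** (2.3.3): "once weekly (Weeks 1-4), then every other week (Weeks 6 and 8), followed by every four weeks (Weeks 12, 16, 20, and 24". Treatment then closes with a Week 26 visit. Weeks 1, 2, 3, 6 and 24 are therefore visits without an NMOS.
- **CM visits** (2.3.2): in the Sustaining Phase they are two to four weeks apart. After a PEth result of 20 ng/mL or more, "CM participants will return to the Starting Phase with weekly visits until PEth levels once again indicate abstinence".
- **Use of the data**: section 3.2 lists use of costly medical care among the additional outcomes analysed by GEE. Section 3.3.2 states that "between-arm difference in predicted-mean costs will be calculated according to each stakeholder perspective", for the intervention and follow-up periods, with cost-effectiveness ratios for each period.

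**The concern.** The anchor and the schedule do not fit together. If a participant is asked about the time since the last visit, and that visit had no NMOS, everything before it goes unasked. The self-reported drinking calendar (2.5.3) uses almost the same anchor, but it is given at each visit, so it leaves no gap. The NMOS is not.

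The unasked time is not the same in both arms. Control visits are fixed. CM visits become weekly when PEth shows drinking, so the literal window is shortest for CM participants who keep drinking. The Discussion itself expects those who cannot sustain abstinence to be seen more often. Loss that depends on arm and on response biases a between-arm comparison. Here it affects treatment-period healthcare utilization and the NMOS-measured part of the cost differences and ratios. An admission or emergency visit in an unasked week cannot reliably be recovered later.

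**Working it through.** **Inputs.** NMOS treatment weeks 4, 8, 12, 16, 20, 26 and follow-up weeks 30, 38, 52, 78 (Table 1). Control visit weeks 1, 2, 3, 4, 6, 8, 12, 16, 20, 24, 26 (2.3.3). CM visits weekly, or every two to four weeks, according to phase (2.3.2). Treatment is counted from Week 0.

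**Check of the calendar.** The article gives no NMOS coverage figure to reproduce. The Control calendar does reproduce the number of in-treatment assessments in section 3.2: 4 + 2 + 4 + 1 = 11.

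**Literal coverage.** Weeks covered = sum over NMOS weeks of (NMOS week minus the week of the visit just before it).

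| Calendar | Wk 4 | Wk 8 | Wk 12 | Wk 16 | Wk 20 | Wk 26 | Total of 26 |
|---|---|---|---|---|---|---|---|
| Control | 1 | 2 | 4 | 4 | 4 | 2 | 17 (65%) |
| CM, weekly throughout | 1 | 1 | 1 | 1 | 1 | 1 | 6 (23%) |
| CM, every two weeks after Week 4 | 1 | 2 | 2 | 2 | 2 | 2 | 11 (42%) |
| CM, every four weeks after Week 4, plus Week 26 | 1 | 4 | 4 | 4 | 4 | 2 | 19 (73%) |

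A CM participant who moves to a Week 6 visit and then returns to weekly visits also has 6 weeks covered.

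**Effect on recorded use.** Suppose true weekly use is equal in both arms, a share q of CM is weekly throughout, and the rest have r weeks covered. Average CM coverage is 6q + r(1 − q), and the apparent shortfall against Control is 1 − [6q + r(1 − q)]/17. The article gives neither q nor r, so both are assumptions.

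| q | r = 17 (Control calendar) | r = 19 (four-weekly) | r = 11 (two-weekly) |
|---|---|---|---|
| 25% | 14.25 weeks, 16% lower | 15.75 weeks, 7% lower | 9.75 weeks, 43% lower |
| 50% | 11.5 weeks, 32% lower | 12.5 weeks, 26% lower | 8.5 weeks, 50% lower |
| 75% | 8.75 weeks, 49% lower | 9.25 weeks, 46% lower | 7.25 weeks, 57% lower |

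With r = 19 the sign reverses when q is below 2/13, about 15%, because 19 − 13q then exceeds 17.

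**Whole study.** The NMOS is given at every follow-up visit, so the windows are 4 + 8 + 14 + 26 = 52 of 52 weeks in both arms. Over 78 weeks Control has 17 + 52 = 69 (88%) and a weekly CM participant 6 + 52 = 58 (74%). Even if every CM participant were weekly throughout, the shortfall is 1 − 58/69 = 16%.

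**With the window anchored to the previous NMOS.** Treatment windows are 4 + 4 + 4 + 4 + 4 + 6 = 26 of 26 weeks, and 26 + 52 = 78 of 78 overall, in both arms.

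**The case against.** The strongest reply is that the loss depends on reading the anchor literally. The article is a condensed account, the form and interviewer instructions are not shown, and the last visit may be meant as the last visit with an NMOS. Nothing would then be lost. This stands as a reason to state the loss conditionally. It does not remove the point: the sentence uses separate words for visits and administrations, the phrase reads as the participant's own prompt, and nothing elsewhere in the article redirects it.

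A reader might infer that CM would look about 32% cheaper. The article does not support that. The 32% is a difference in recorded NMOS weeks when half of CM is assumed weekly throughout and the rest are assumed to follow the Control calendar. It moves in both directions with those assumptions. It is also not a difference in total cost. The NMOS covers resources outside the study (2.5.4), while intervention costs come from microcosting and enter the healthcare-sector perspective (3.3.2). It further presumes that recorded use is summed with no adjustment for window length, a detail that the unseen analysis plan may settle.

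A reader might also infer that most resource use of CM participants who drink is lost from the trial. On the literal reading that holds only within the 26 treatment weeks and only for those kept on weekly visits. Control loses 9 of 26 weeks too, so the bias comes from the difference between arms.

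Complete follow-up data do not settle the matter either, because section 3.3.2 reports costs and ratios separately for the treatment period.

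**Conclusion.** The recall anchor in section 2.5.6 and the NMOS schedule in Table 1 contradict each other in effect. Followed as written, they cover 17 of 26 treatment weeks in Control and 6 of 26 for a CM participant seen weekly throughout. NMOS-measured use would be under-recorded most in CM participants who keep drinking. If use is summed without rescaling, the treatment-period utilization comparison and the NMOS part of the cost differences and ratios are biased in CM's favour, unless few CM participants stay weekly and the rest are seen four-weekly.

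On the Control-calendar assumption the shortfall is 16% to 49% for weekly shares of 25% to 75%. It is at most 16% over 78 weeks. These figures assume equal true use and the literal window.

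The primary PEth outcome is untouched, and follow-up windows have no gap. Severity is moderate: it concerns the economic and healthcare-utilization aims. The case for acting now is that unasked weeks cannot be reliably filled in afterwards.

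**What to change.** Reconcile section 2.5.6 with Table 1. Anchor every NMOS administration after enrollment to the previous NMOS interview, with that date shown to the participant, and record the start and end dates of each recall window. The recorded dates also allow the week between enrollment and randomization to be set apart from treatment time.

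For any data already collected under the visit anchor, analyse use per recalled day. This corrects average rates only if the weeks asked about are representative, and it does not recover events in unasked weeks.

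The cost is one line on the form and an interviewer prompt. Recall lengthens to about 4 to 6 weeks during treatment, within the 4 to 26 weeks already used in follow-up. If the sponsor already intends this window, stating it in section 2.5.6 and confirming the form's prompt is enough.

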#### Implementation measures

2.5.7.

The percentage of visits missed will serve as an indicator of attrition. Additionally, we will track the frequency of, and reason for, delayed PEth sample shipments. If a sample is shipped 1–7 days after the study visit, instead of the same say as the study visit, it will be coded as “late.” If a sample is not shipped within 7 days, it will be coded as missing, the reinforcers withheld, and reinforcers reset to $20 when the next PEth negative sample is received. To assess participant satisfaction for this study, we will administer CM participants the Client Satisfaction Questionnaire, in which an a priori mean score >23 will indicate overall satisfaction with our telehealth-based CM procedures [32].

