If CM participants have an unexcused missed visit or do not ship their sample within a week of the study visit, the PEth sample will be considered positive. In such cases, reinforcers will be withheld, and the participant will return to the Starting Phase. The maximum CM reinforcer that can be earned per week of abstinence is $90 (e.g., for visits occurring once every 4 weeks the max is $360). The maximum total amount that can be earned for negative PEth results during the CM intervention is $1,820.

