## Discussion

4.

This randomized controlled clinical trial assesses the efficacy of a telehealth-based CM intervention for AUD in a large national sample. Telehealth delivery has some potential limitations, such as access to and comfort with technology, but advantages, like reduced stigma and travel, likely outweigh the disadvantages. For instance, 64% of participants in our telehealth-based CM pilot study were treatment-naïve [7], suggesting that telehealth interventions might be a low-burden and low-barrier treatment option for individuals with AUD.

While CM is an evidence-based treatment for AUD and a powerful tool for initiating abstinence, evidence for sustained post-intervention effects is less conclusive [23,47,48,52,56]. In efforts to address this gap in CM research, the follow-up period for this study is 12 months in duration compared to 6 months in traditional CM models. Another strength of this study is the utilization of the ANA framework and alcohol biomarkers to identify potential predictors of treatment response and long-term outcomes. These predictors could provide opportunities to improve treatment efficacy and better direct care for this population (e.g., individualized treatment approaches). Lastly, this study will fill a critical gap in the CM literature by providing essential information for providers regarding resource and cost requirements for implementing this telehealth-based CM model.

A limitation of the study is that there is up to a one-week delay between submission of blood samples and provision of CM reinforcers. If we do not observe an effect of CM on outcomes, it could be a result of this delay. However, in our pilot study, CM participants did not report concerns regarding the week delay (i.e., surveys and qualitative interview) and achieved levels of alcohol abstinence consistent with previous CM studies [7]. Another potential limitation is the increased burden for the CM group, depending on how long participants remain in the Starting Phase. More visits might contribute to higher attrition in the CM condition, or it could lead to lower levels of attrition because individuals who are unable to achieve long-term abstinence (i.e., <20 ng/mL) will have more frequent visits and a lower bar for achieving reinforcers. The effects of an adaptive reinforcement schedule on attrition rates in the CM group will be assessed.

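### Attrition is scored as the percentage of visits missed, but the number of visits due depends on arm and attendance, so the same mid-treatment dropout can score worse in CM than in Control

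*Protocol article*

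**What the plan says.** Section 2.5.7 (Implementation measures) names the measure: "The percentage of visits missed will serve as an indicator of attrition". Table 1 lists it as percent missed visits, ticked in the *Every Visit* column.

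The visits due differ by arm:

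- **Control (Section 2.3.3).** A fixed calendar: Weeks 1, 2, 3, 4, 6, 8, 12, 16, 20 and 24, with "a last intervention visit occurring on Week 26".
- **CM (Section 2.3.2), doing well.** After the Starting Phase, "participants will transition to the Sustaining Phase with visits every two to four weeks, as long as abstinence is maintained".
- **CM, after a positive result.** "CM participants will return to the Starting Phase with weekly visits until PEth levels once again indicate abstinence".
- **CM, after non-attendance.** The rule begins "If CM participants have an unexcused missed visit or do not ship their sample within a week of the study visit". The sample then counts as positive, "reinforcers will be withheld, and the participant will return to the Starting Phase". Treatment still ends at Week 26.

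The Discussion notes that extra CM visits might raise or lower attrition, and promises: "The effects of an adaptive reinforcement schedule on attrition rates in the CM group will be assessed".

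**The concern.** A percentage of visits missed compares arms fairly only if the visits due are the same in both, or at least do not respond to missing. Here they respond in one arm only. A CM participant who stops attending sends no sample, so cannot show PEth below 20 ng/mL and, on the stated rules, cannot leave weekly scheduling. Each later week to Week 26 adds a visit to both numerator and denominator. A Control participant who stops on the same day adds only the remaining fixed visits, which after Week 4 fall mostly two to four weeks apart.

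The Discussion asks whether the adaptive schedule changes attrition. The indicator moves with the schedule even when nobody's behaviour differs. Equal dropout could be read as schedule-driven dropout in CM, and a real retention benefit could be hidden.

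**Working it through.** **Inputs.** The Control calendar is from Section 2.3.3 and the CM rules from Section 2.3.2. The follow-up visits (Weeks 30, 38, 52, 78) are from Section 2.1. The 25% reduction for attrition in Section 3.5 is used only for an arm-level illustration.

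**Check against the article.** The Control calendar has 4 + 2 + 4 + 1 = 11 visits, which matches the 11 in-treatment assessments in Section 3.2. The article gives no figure for missed visits by arm.

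**Formulas.** Let *w* be the last attended week, with permanent dropout afterwards.

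- Control: (calendar visits after *w*) / 11.
- CM case A, on Sustaining visits at dropout: attended visits are assumed to follow the Control calendar. The next calendar visit is missed, then one visit is due and missed every week to Week 26.
- CM case B, on weekly visits throughout: (26 − *w*) / 26.

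Example, *w* = 8, case A: six visits attended, Week 12 missed, then Weeks 13-26 missed. That is 15 missed of 6 + 15 = 21.

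| Last attended | Control | CM case A | A − Control | CM case B | B − Control |
|---|---|---|---|---|---|
| Week 1 | 10/11 = 90.9% | 25/26 = 96.2% | +5.2 | 25/26 = 96.2% | +5.2 |
| Week 4 | 7/11 = 63.6% | 21/25 = 84.0% | +20.4 | 22/26 = 84.6% | +21.0 |
| Week 6 | 6/11 = 54.5% | 19/24 = 79.2% | +24.6 | 20/26 = 76.9% | +22.4 |
| Week 8 | 5/11 = 45.5% | 15/21 = 71.4% | +26.0 | 18/26 = 69.2% | +23.8 |
| Week 12 | 4/11 = 36.4% | 11/18 = 61.1% | +24.7 | 14/26 = 53.8% | +17.5 |
| Week 16 | 3/11 = 27.3% | 7/15 = 46.7% | +19.4 | 10/26 = 38.5% | +11.2 |
| Week 20 | 2/11 = 18.2% | 3/12 = 25.0% | +6.8 | 6/26 = 23.1% | +4.9 |
| Week 24 | 1/11 = 9.1% | 1/11 = 9.1% | 0.0 | 2/26 = 7.7% | −1.4 |

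**Average over dropout time.** With dropout spread evenly over Weeks 0-25, the mean gap is +16.5 points (A) or +9.3 points (B).

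**Other Sustaining calendars.** If case A visits run strictly every two or every four weeks from Week 4, the peak is 28.5 or 29.5 points, so the exact maximum depends on a calendar the article leaves open.

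**Follow-up visits included.** Table 1 ticks PEth only under *Enrolment Visit* and *Every Visit*, yet Section 3.2 analyses PEth at follow-up, so *Every Visit* covers follow-up. Adding four missed visits to both arms (case A):

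- Week 4: 25/29 = 86.2% v 11/15 = 73.3%, +12.9.
- Week 8: 19/25 = 76.0% v 9/15 = 60.0%, +16.0, the largest gap.
- Week 12: 15/22 = 68.2% v 8/15 = 53.3%, +14.8.

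**Arm level.** With 25% dropout spread evenly and percentages averaged by person, the gap is 0.25 × 16.5 = 4.1 points (A) or 0.25 × 9.3 = 2.3 (B). The article does not say whether visits are averaged by person or pooled. As a pooled illustration near the peak, let 25% of each arm drop out after Week 8 and the rest attend 11 visits. CM misses (0.25 × 15)/(0.25 × 21 + 0.75 × 11) = 3.75/13.5 = 28%, and Control misses 1.25/11 = 11%.

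**Single miss, then return.** With one extra weekly visit attended, CM scores 1/12 = 8.3% against 1/11 = 9.1% (−0.8 points). With four extra it scores 1/15 = 6.7% (−2.4 points).

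**Common weeks.** Scored on the same 11 weeks, dropout after Week 8 is 5/11 = 45.5% in both arms, and the gap is zero.

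**The case against.** The strongest reply has four parts.

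1. *The gap rests on an assumption.* Nothing says that a participant who has left keeps accruing weekly missed visits, and only unexcused misses trigger the return. This stands as a condition on every figure above. Still, the CM rules give no other exit from weekly visits for someone who sends no sample.
2. *The denominator is a detail for the full protocol or SAP, and Section 3.2 already speaks of 11 assessments without separating arms.* Scoring on those 11 is compatible with the text. But Section 2.5.7 and Table 1 do fix an indicator, and Table 1 ties it to every visit. Followed as written, it depends on arm.
3. *No between-arm test is planned.* A reader might infer a formal CM-versus-Control comparison of this percentage. The Discussion does not say so: it refers to attrition in the CM group, and Section 2.5.7 offers one indicator, not the only one possible. Even so, an effect of the adaptive schedule is hard to judge without reference to the arm that lacks it.
4. *The consequence is small.* A reader might also infer that the efficacy results are biased, or that the handling of missing data is compromised. The article does not support this. No efficacy model uses the percentage, and Section 3.4 plans maximum likelihood or multiple imputation with missing-not-at-random sensitivity analyses, none of which is linked to it. This part stands in full.

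**Conclusion.** The concern holds in a limited form. As described, the indicator has a denominator that differs by arm and grows with non-attendance in CM only, and this confounds the promised assessment of the adaptive schedule.

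A general gap of 20-25 points for any dropout is tempting to infer but wrong. That size belongs to mid-treatment dropout counted on treatment visits alone: about 19-26 points after Weeks 4-16 from the Sustaining Phase, or 21-24 points after Weeks 4-8 on weekly visits. The gap is smaller early, near zero or slightly reversed late, at most about 16 points with follow-up included, and slightly reversed for a single miss with return. At 25% dropout it is about 4 points per arm when averaged by person.

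These figures assume that weekly visits continue to be counted after dropout, that the misses are unexcused and, in case A, that CM visits before dropout follow the Control calendar. The point concerns an implementation measure. It is worth correcting, but it does not threaten the trial's efficacy conclusions.

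**What to change.** In Section 2.5.7, and in the SAP if it repeats the measure, define attrition for any between-arm statement on the weeks common to both arms: Weeks 1-4, 6, 8, 12, 16, 20, 24 and 26, plus follow-up Weeks 30, 38, 52 and 78. Report the proportion of these with no visit or sample, and the time to last attended visit. Two details should be settled in the same text:

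- the window around each common week, since a CM participant's visits may fall off this calendar after a return to weekly visits;
- that time to last attended visit is read on the common weeks, so that more frequent CM visits do not lengthen it.

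Report the percentage of all CM visits missed only as a within-CM burden measure, and say whether it is averaged by person or pooled over visits. The cost is a few sentences. No new data or visits are needed, and the treatment schedule does not change.
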